### Participants

We will recruit adults (≥18 years of age), who present to emergency public health facilities (district hospitals, primary or community health centers) in Balod and Rajnandgaon districts with attempted suicide or are already admitted for attempted suicide within one week of the study start date. We will exclude individuals who are unable to communicate clearly due to medical conditions or speech/hearing disabilities despite reasonable accommodations, those unable to comprehend one of the local languages used by CHOs to deliver the intervention, and individuals who do not reside within the catchment area of Balod and Rajnandgaon Health and Wellness Centers (where trained CHOs are placed).

### Study interventions

CASP was developed specifically for individuals at risk of suicide by SNEHA Suicide Prevention Center (Chennai, India)
^
8
^ and incorporates two evidence-based components: brief contact
^
7,
11
^ and safety planning.
^
9
^ Its core focus revolves around establishing periodic connections with individuals who have recently survived suicide attempts, alongside a collaborative effort to create and track progress using personalized safety planning cards intended for distressing as well as crisis situations. Within this framework, emergency nurses will report details (name of health facility, age and gender of participant) to the project team who communicate this to Community Health Officers (CHOs) from that locality. A nearby CHO will then follow up with and visit the consenting individual at a time and place of their choosing, within the upcoming week. The timing of these visits will adhere to the contact schedule outlined in the multi-site WHO suicide study, SUPRE-MISS (1, 2, 4, 7, and 11 weeks after the attempt).
^
10,
12
^ During these visits, CHOs will extend emotional support, gauge the level of risk, and jointly work with the individual to identify personal warning signs, coping strategies, and available support mechanisms (safety planning).

Safety planning
^
8,
9
^ will be carried out by the CHO with the participant in a quiet and confidential setting after each participant has received their own safety planning card. Safety planning will be a collaborative exercise wherein the CHO will guide the participant through each step involved in safety planning and help the participant to fill in the card. Participants will be encouraged to refer to their safety planning card when they are distressed, and their use will be monitored during visits. The primary objective of the safety planning card is to support participants when they experience suicidal thoughts and urges by reminding them of coping mechanisms that make them feel better, people they can reach out to and actions they can take to make their environment safer.

Referrals to social benefits: Many suicides occur spontaneously in periods of crisis where there is a breakdown in coping mechanisms for life stressors, such as financial difficulties, sudden illness or managing a chronic illness, relationship difficulties, etc. According to the National Crime Records Bureau (2022), family issues and illness are the main contributors to suicide in India, accounting for 32% and 18% of all suicides in 2022 respectively, while ‘Unemployment’ accounted for 1.9% and ‘Bankruptcy or indebtedness’ accounts for 4.1% suicides.
^
4
^ Thus, increasing access to state provided social benefits and schemes which focus on unemployment and livelihood support can help address some of these risk factors. CHOs will be trained to refer individuals in need of social security and support (e.g., government-provided employment or pension benefits, disability schemes, etc.) to the appropriate government workers, and all CHOs will have a list of locally available schemes and programs which they can use to match people to schemes and provide further information during visits.

### Control condition: Enhanced Usual Care (EUC)

In Chhattisgarh, usual care under the DMHP includes a telephonic follow-up, where a social worker or a clinical psychologist at the DMHP clinic provides counselling for an individual who has recently attempted suicide, and invites them to visit the DMHP clinic in person to receive continued support. However, some clinics (such as in as our intervention districts) do not have any existing follow up care for suicide due to staff shortages, and so the CASP pathway will serve as the primary follow-up response in these districts. In the control districts, participants will receive Enhanced Usual Care (EUC). EUC will consist of the usual care provided by the District Mental Health Plan (DMHP) in Balodabazar and Mungeli, which have an active DMHP program staffed by a social worker, a nurse as well as a psychiatric nurse, a clinical psychologist and a Medical Officer (MO) (a medical professional based in primary and community care clinics). DMHP personnel in control districts are trained in telephonic counselling for mental health and suicide which they apply while carrying out follow-up calls for suicide attempts. Moreover, the DMHP in the control districts carry out monthly mental health awareness raising camps in the community to increase awareness around mental health and their services (this is not occurring in the intervention districts). The CASP team will also provide a brief training with DMHP staff in control districts covering suicide, its prevalence and associated risk factors, and myth busting around suicide prevention.

### Recruitment & Retention

Individuals presenting at district hospitals, Primary Health Centres (PHCs), or Community Health Centres (CHCs) following a suicide attempt will be identified by casualty nurses, who will screen for eligibility and invite those meeting the criteria to participate in the study. After providing a brief explanation of the study, the nurses will obtain verbal consent from interested individuals and notify the research team via telephone, sharing details such as the participant’s village of residence and hospital discharge date.

The research team will then assign a Community Health Officer (CHO) from the nearest Health and Wellness Center to follow up with the participant at a time and place of their convenience. Within one week of discharge, the CHO will meet the participant, obtain written informed consent, and initiate follow-up care as per the CASP intervention protocol.

During the informed consent process, the CHO will explain the study’s purpose, procedures, and the potential risks and benefits of participation, emphasizing that involvement is entirely voluntary. Participants will receive a consent form and an information sheet detailing the study objectives, procedures, and the contact information of CASP research team members, enabling them to seek clarifications or address concerns at any point during the study.

To support participant retention in the study, we will make up to five contact attempts over a two-week period following each scheduled follow-up appointment. These attempts will include a combination of telephone calls and in-person home visits (where feasible and safe).

If a participant misses a follow-up but can be contacted later, they will still be approached for subsequent follow-ups at later time points.

For participants who actively request to discontinue follow-ups, the study team will first explore and address any concerns to encourage continued participation. However, if the participant continues to decline, they will be formally withdrawn from the intervention and no further contact will be made.

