^ and is recommended by the World Health Organisation (WHO) as an effective intervention to reduce suicides and attempted suicides in the general population.
^
13
^ Safety planning interventions have been found to reduce fatal and non-fatal suicide attempts in a recent meta- analysis
^
9
^ and when tested in conjunction with brief contact among veterans in the US.
^
14
^ Leveraging the public health system to deliver CASP may be a promising solution to address the treatment gap for suicide in Chhattisgarh and similarly low-resourced settings, however, the feasibility and acceptability of a health-systems approach for CASP is yet to be determined.

This study will integrate CASP into the public health system by training non-specialist health workers to identify and follow up with adults who have recently attempted suicide in two districts where the DMHP is not providing any response to suicide attempts (due to personnel shortages). We will train two groups of health workers: (1) nurses in emergency wards of health centres to identify and recruit adults who have attempted suicide from emergency wards, and (2) Community Health Officers (CHOs) at community-based Health and Wellness Centers (HWCs) to deliver the CASP intervention in the community over an 11-week follow-up period.

Follow ups by CHOs will include suicide risk assessments, provision of emotional support and empathetic listening, and collaborative safety planning to identify steps a participant can follow if they are in distress. Steps include identifying symptoms of distress, recognizing coping mechanisms and planning for future use of coping strategies, activating support networks, referrals for professional care and sharing details of the nearest emergency services. The first follow up visit will occur within one week of discharge from a healthcare facility post-attempt, and then continue periodically over the immediate 11-week period afterward.

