### Data collection

Baseline demographic data—including age, gender, education, marital status, employment status, caste/tribal background, income, and contact details—will be collected by Community Health Officers (CHOs) from consenting participants. Study records will include the following: (1) record books maintained by nurses at health facilities, documenting the date, age, gender, method of attempt, verbal consent status, and, if applicable, reasons for refusal; and (2) CHO records detailing the dates and locations of participant visits to monitor adherence to the CASP intervention schedule (at 1, 2, 4, 7, and 11 weeks post-attempt).

For outcome assessments, the Columbia-Suicide Severity Rating Scale (C-SSRS) and the Patient Health Questionnaire-9 (PHQ-9) will be administered to participants in the intervention group at baseline and during follow-ups at 6 and 12 months. Within the control arm, a brief follow up survey will be administered that captures suicide re-attempt at 6 and 12 month follow up points. Data collection will be conducted by trained data collectors, who are local Master’s graduates in mental health or related fields with prior experience in the health system.

To support the cost analysis and economic evaluation, a brief cost survey (Modified TiC-P) and the EuroQol-5D-5L will be administered to a random sample of 50 participants in both the intervention and control groups at baseline and at the 6-month follow-up. Data collection will be conducted using paper-and-pencil assessments or self-administered forms, based on participant preference.

Qualitative follow-up data will be collected through in-depth and semi-structured interviews, lasting approximately one hour each. These interviews will be conducted by research team members and audio recorded with prior informed consent for transcription purposes. Acceptability interviews with participants will include a random sample selected independently of intervention completion status, ensuring the inclusion of individuals who may have dropped out of the study. See
Figure 1 for research and data collection procedures.

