The economic evaluation will constitute a cost-utility analysis with QALYs as central outcome. To simultaneously evaluate both costs and outcomes, baseline-adjusted seemingly unrelated regression equations (SURE) models will be used. Given that costs are usually non-normally distributed the SURE models will be bootstrapped (2,500 times). To allow for intention to treat analysis, single imputation (based on predictive mean matching) nested in each bootstrap simulation will be used, as recommended by Brand and colleagues.
^
34
^ For each bootstrap simulation, incremental cost-effectiveness ratios (ICERs) will be calculated by dividing the incremental costs by the incremental QALYs, resulting in the costs per QALY gained. Next, ICERs will be plotted on a cost-effectiveness plane and a cost effectiveness acceptability curve (CEAC) will be constructed to determine the probabilities that the new intervention is cost-effective given a range of WTP values for a QALY.
^
35
^ Given the lack of formal WTP thresholds, a WTP ceiling of three times the national annual gross domestic product (GDP) per capita has been recommended.
^
36
^ Sensitivity analyses will be directed towards the main drivers of costs and QALYs.

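### The withdrawal rule ties refusing CASP visits to ending all contact, so decliners' 6- and 12-month outcomes can be lost by a route that exists only in the CASP arm

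*Protocol article*

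**What the plan says.** The Recruitment & Retention section of the protocol article treats two groups differently.

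- People who miss a follow-up but can be reached later: "they will still be approached for subsequent follow-ups at later time points".
- People who refuse. The rule opens "For participants who actively request to discontinue follow-ups". The team first tries to resolve their concerns. If they still decline, "they will be formally withdrawn from the intervention and no further contact will be made".

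The article uses the word follow-up in two senses. In the Introduction it means the community health officer (CHO) visits: "Follow ups by CHOs will include suicide risk assessments, provision of emotional support". Under Secondary outcome measures and Data collection it means the 6- and 12-month assessments.

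The CHO visits take place at "1, 2, 4, 7, and 11 weeks after the attempt" (Study interventions), in the CASP districts only. In the control districts, "EUC will consist of the usual care provided by the District Mental Health Plan (DMHP) in Balodabazar and Mungeli", with telephone follow-up. Data collection has C-SSRS and PHQ-9 in the intervention group at baseline, 6 and 12 months, and a short re-attempt survey in controls at 6 and 12 months. For the acceptability interviews it draws a random sample regardless of completion status, "ensuring the inclusion of individuals who may have dropped out of the study".

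**The concern.** The first half of the rule describes stopping an intervention, and the second half ends contact altogether. The two are different events. Someone may be tired of home visits yet willing to answer a short interview at month 6. The rule never asks which of the two is being refused.

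All five visits fall before month 6, so every refusal of a visit comes before both outcome assessments. Three things are at stake:

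- **Re-attempt comparison.** This is the one clinical outcome compared between arms. It loses people who may differ in risk from those who stay, by a route that controls do not have.
- **Acceptability.** This is a primary outcome, and active decliners are among the most informative people to interview.
- **Retention criterion.** Progression requires under 30% loss at the 6-month data collection. The rule would count refusal of visits as loss to assessment, so the pilot could not tell the two apart.

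**Working it through.** **What the text implies**

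1. *Does any other section restore outcome collection for active decliners?* No. Later re-approach is stated only for people who miss a follow-up without refusing. No other source of a decliner's outcome is given.
2. *Does the double meaning of follow-up matter?* If it means CHO visits, refusing visits ends the outcome interviews as well. If it covers visits and assessments, the rule does not ask which is refused. Either way, no further contact excludes the 6- and 12-month interviews on its plain reading.
3. *Is the route the same in both arms?* No. Controls have no CHO visits to refuse. They can refuse a telephone call or a survey, so loss is possible in both arms, but loss set off by refusing CASP visits is not.
4. *Does the rule fit the acceptability sample?* For passive drop-outs, yes, because they may still be approached. For active decliners, no.

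**How large the bias could be**

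The documents give no refusal rate and no risk for decliners, so the plan has no figure to reproduce here. What follows is an illustration.

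Assumed inputs:

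- True re-attempt risk is 10% in both arms. The 10% is the control rate in the Sample size section; equality between arms is an assumption, so that any difference is spurious.
- A share w of the CASP arm declines: 10% or 20%, which is 25 or 50 of 250.
- Decliners have RR times the risk of stayers.
- Controls have no comparable loss.

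The true risk is a mixture: 0.10 = (1 − w)·q + w·RR·q. The risk observed among stayers is therefore q = 0.10 / [(1 − w) + w·RR], and the spurious benefit is 0.10 − q.

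| w | RR | q | Spurious benefit (points) |
|---|---|---|---|
| 10% | 2 | 0.10/1.10 = 9.1% | 0.9 |
| 10% | 3 | 0.10/1.20 = 8.3% | 1.7 |
| 20% | 2 | 0.10/1.20 = 8.3% | 1.7 |
| 20% | 3 | 0.10/1.40 = 7.1% | 2.9 |
| 10% or 20% | 1 | 0.10/1.00 = 10.0% | 0 |
| 10% | 0.5 | 0.10/0.95 = 10.5% | −0.5 |
| 20% | 0.5 | 0.10/0.90 = 11.1% | −1.1 |

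If controls lost the same share with the same RR, both arms would show the same q and the spurious difference would be zero. What matters is the difference between arms in selective loss.

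Bounds need no assumed RR. If 20% of the CASP arm is missing and 10% of the rest re-attempt, the arm's risk lies between 0.10 × 0.80 = 8% (no missing person re-attempts) and 0.08 + 0.20 = 28% (all do).

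**The case against.** **The rule may end only the intervention.** It says withdrawn from the intervention, not from the study. Contact often denotes CASP delivery in this article, and outcomes are gathered by separate data collectors. On that reading outcome collection stays open. This has some force, and it is why the point is about a rule that needs splitting and not about outcomes certain to be lost. But the same section describes contact attempts as a means of keeping participants in the study, and the refusal rule speaks of encouraging continued participation. The wide reading is the plain one, and staff following it would stop all contact.

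**A refusal must be respected.** It must, and nothing here argues otherwise. The point concerns people who refuse visits but might accept an interview.

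**Stronger readings that the documents do not support.** A reader might infer any of these:

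- *A contradiction with intention to treat.* The phrase "To allow for intention to treat analysis" introduces imputation, so it presupposes missing data. It belongs to the economic evaluation, which uses a sub-sample of 100, and not to the re-attempt comparison.
- *Loss in the CASP arm alone.* Controls can also decline, and the rule is not expressly confined to CASP participants.
- *A flat contradiction with the acceptability sample.* Interviewing passive drop-outs satisfies that sentence. The tension covers active decliners only.
- *A bias that favours CASP.* People who decline because they feel well would push it the other way.

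**This is a pilot.** Re-attempt is a secondary outcome in a non-randomised study, and 20% loss is already allowed for. That limits the weight of the point but does not remove it: an allowance for loss protects power and does nothing about selective loss.

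**Conclusion.** The point holds in a limited form. As written, the rule joins two decisions that should be separate. It gives up outcomes that could have been obtained, from people who refuse CASP visits, and no other section recovers them. An analysis plan could not do so either, since the data would not have been collected.

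The consequence is a possible difference between arms in who is missing, with bias in the re-attempt comparison in either direction. Its size cannot be computed from the documents. The 0.9 to 2.9 points of spurious benefit rest wholly on the assumed shares, the assumed risk ratios of 2 to 3 and the absence of comparable loss in controls. The bias is zero at equal risk and changes sign below it. That the loss would be selective is a reasonable inference, not something the article states.

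**What to change.** Replace the single rule with two categories:

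- **(a) Stops CASP visits.** No further CHO visits, but the participant is asked whether the 6- and 12-month outcome interviews and the acceptability interview may still take place. The participant is analysed in the CASP arm.
- **(b) Withdraws from the study.** No further contact, with data up to that date kept.

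Apply (b) identically in both arms. Report the number in each category by arm, including those already withdrawn under the present wording.

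The cost is a change to the protocol text and the withdrawal form, and an ethics notification while the study is running. The article gives recruitment and follow-up as ongoing, with data collection ending in November 2025, so the change helps only participants not yet withdrawn. For those already withdrawn, the counts by arm are what can still be reported.

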### Sample size

Since the present study is a pilot study (focused primarily on understanding feasibility and refining processes in anticipation of a full-scale trial), the sample size calculation is based on a conservative assumed rate of the secondary outcome (change in suicide attempts) of 10% at the end of 12 months in the control group. Thus, a minimum enrolment of 500 participants (250 control; 250 intervention) has a power of 80% (at a 2-sided alpha level of 0.05) to detect an absolute risk reduction of 10 percent points (minimal detectable difference of 10% between the groups (intervention and control), while allowing for an expected 20% loss to follow-up over the 12 months follow-up period.

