### Data analysis

*Implementation outcomes*

Descriptive statistics (means, medians and standard deviations) of the reach, adoption and implementation metrics will be calculated. Qualitative thematic analysis
^
27
^ of the in-depth interviews exploring feasibility and acceptability will be carried out using a mix of inductive and deductive approaches. Two coders will independently review transcripts, generate initial codes, and collaboratively develop a comprehensive codebook (initial coding). This will be followed by a pilot coding phase to ensure procedural consistency before independent coding of the remaining transcripts, with discrepancies resolved through consensus or third-rater consultation. Researchers will then interpret and refine final themes. Coding will be done using NVivo 1.4.1.

*Clinical outcomes*
1.Difference in percentage of re-attempted suicide and death by suicide

We will analyze the difference between the intervention and control group in the percentage of participants who, after initial visit in the hospital for a suicide attempt, have re-attempted suicide (including deaths by suicide) at 6 and 12 months of follow-up. For statistical analysis, we will use Bayesian binominal testing as implemented in the open software program JASP.
^
28
^ Bayesian analysis allows us to not only test whether the null hypothesis is true or false, but also to test how likely the alternative hypothesis (that the change in suicide rates between intervention and control) is given the data.
^
29,
30
^
2.Change in depression, suicide risk and TiC-P scores

The mean change in depression and suicidal behavior scores between baseline and 6-
and 12-
months follow-up within the intervention group will be calculated using Bayesian linear mixed models as implemented in JASP. Models will be estimated both with and without a random effect for location, to see if it is needed to control for any clustering effect.
^
31
^
3.Quality of life

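### The sample size rests on 80% power at a two-sided alpha of 0.05, but the only test planned for re-attempt is Bayesian, so the stated power and alpha do not describe the planned analysis

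*Protocol article*

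**What the plan says.** **Protocol article, Sample size.** The calculation assumes a re-attempt rate "of 10% at the end of 12 months in the control group". It enrols 250 participants per arm, allows for 20% loss over 12 months, and states that this "has a power of 80% (at a 2-sided alpha level of 0.05) to detect an absolute risk reduction of 10 percent points".

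**Protocol article, Data analysis, Clinical outcomes, item 1.** The percentage re-attempting (suicide deaths included) is compared between the two groups at 6 and 12 months. For this, "we will use Bayesian binominal testing as implemented in the open software program JASP". The reason given is that "Bayesian analysis allows us to not only test whether the null hypothesis is true or false", and that it also shows how likely the alternative is given the data. No significance test at any alpha is planned for this outcome.

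**Status of the outcome.** Under Aims and Outcomes, re-attempt is secondary; the primary outcomes concern implementation.

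**The concern.** Power and alpha belong to a particular test with a particular rejection rule. The article fixes both halves of its design affirmatively: a two-sided 0.05 level with 80% power in one section, and a Bayesian test in another. The two do not belong to the same procedure.

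A reader who meets an inconclusive Bayesian result will weigh it as the product of a study with an 80% chance of showing the target effect. That chance was never worked out for the analysis to be run. The mismatch would remain if the assumed rates were corrected, and also if the test were specified as a two-sample Bayesian comparison.

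**Working it through.** **Inputs from the Sample size section:** two-sided alpha 0.05; power 80%; control rate 10%; absolute reduction 10 points; 250 per arm; 20% loss, so 250 × 0.8 = 200 evaluable per arm.

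**Step 1. Where the 80% comes from.** For the pooled two-proportion z-test with difference d and mean rate p̄:

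power ≈ Φ{ [d√n − 1.96 √(2p̄(1−p̄))] / √(p₁(1−p₁) + p₂(1−p₂)) }

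- *Literal rates, 10% against 0%.* p̄ = 0.05, n = 200: (1.414 − 1.96 × 0.3082) / 0.3 = 2.70, so power is 99.7%. For 80% power, 74 per arm would be enough (93 after dividing by 0.8). The stated figure does not follow.
- *10% as the lower of two rates, 20% against 10%.* p̄ = 0.15, n = 200: (1.414 − 1.96 × 0.5050) / 0.5 = 0.849, so power is 80.2%. The required n is (1.96 × 0.5050 + 0.8416 × 0.5)² / 0.01 = 199 per arm, and 199 / 0.8 = 249. This matches the plan. Exact enumeration gives 81.1%.

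The 80% is therefore a frequentist two-proportion figure for 20% against 10%.

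**Step 2. What a Bayesian test would deliver at the same contrast.** The article gives no prior, threshold or sidedness, so the following are assumptions. All pairs of event counts (x₁, x₂) with 200 per arm were enumerated and weighted by their binomial probabilities.

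- *Uniform priors:* BF₁₀ = B(x₁+1, n−x₁+1) · B(x₂+1, n−x₂+1) / B(x₁+x₂+1, 2n−x₁−x₂+1), where B is the beta function.
- *Logit-normal:* N(0,1) priors on the grand log odds and on the log odds ratio; BF₁₀ is the ratio of marginal likelihoods with and without the log odds ratio.

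Probability of meeting the rule, true rates 20% against 10%:

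| Rule | Uniform priors | Logit-normal |
|---|---|---|
| Two-sided BF > 3 | 56.5% | 70.6% |
| Two-sided BF > 10 | 39.6% | 51.1% |
| One-sided BF > 3 | 67.1% | 81.3% |
| Posterior probability of benefit > 0.975 | 80.6% | not computed |

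A one-sample reading, testing the CASP arm against a fixed 20%, gives 85.5% for a two-sided BF > 3, but it ignores sampling error in the control arm.

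**Step 3. The error rate.** With both arms at 10%, a two-sided BF > 3 occurs in 0.6% (uniform) or 2.3% (logit-normal) of studies. Neither rule operates at alpha 0.05.

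**Step 4. The literal rates.** At 10% against 0% with 200 per arm, both two-sample Bayes factors exceed 3 with probability at least 99.9%, and exceed 10 with probability at least 99.6%. The posterior-probability rule is met essentially always.

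**The case against.** The strongest reply is that any shortfall is produced by the assumed rule. A prior, an evidence threshold and sidedness are details that a condensed article may leave to its analysis plan, so their absence is not a fault. This stands. The point does not rest on that absence; it rests on two statements the article does make, which concern different procedures.

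Two stronger readings are tempting, and the documents support neither.

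- *The planned test has only 57-71% power.* That range needs a 20% control rate, against the stated 10%, together with a two-sided rule, a cut-off of 3 and the two assumed priors. Other Bayesian rules at the same contrast give about 81-86%, and the literal rates give nearly 100%. A figure below 80% is possible but not established.
- *A Bayes factor favouring the null would block the definitive trial.* The Progression criteria section and its Table 2 use recruitment, loss to follow-up, retention of health officers, and qualitative feasibility and acceptability. The re-attempt comparison plays no part. At 10% against 5% with uniform priors, the Bayes factor does favour the null by more than 3 in 46.4% of studies. With the logit-normal prior it does so in 0.6%, and a 5-point effect is not one the plan claims to detect. The frequentist test has only 47.5% power there (normal formula), so missing that effect is largely a matter of sample size.

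It is also fair to say that sizing a pilot's secondary outcome with a frequentist formula is common shorthand. That lowers the stakes but does not make the sentence correct for the planned analysis.

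**Conclusion.** The mismatch is real and is settled by the text: "has a power of 80"% and "at a 2-sided alpha level of 0.05" are properties of a two-proportion significance test, while the only analysis planned for re-attempt is Bayesian. How far the true figure lies from 80% cannot be read from the article. Assuming 20% against 10% and 200 evaluable per arm, the two-sample rules examined run from about 40% to 81%. Since one sample size gives so wide a spread, the stated 80% tells the reader little about the planned test.

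The consequence is possible misreading of a secondary, preliminary-effectiveness result. Neither the progression decision nor the conduct of the study is affected. That the stated control rate and target difference imply a CASP rate of 0% is a separate fault in the same sentence, and it must be resolved before any new figure is calculated.

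**What to change.** First reconcile the control rate and the target difference in the Sample size section. Then do one of the following:

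- **(a)** In Data analysis, name a two-sided comparison of two proportions (risk difference with 95% confidence interval) as the analysis the power statement refers to, and report the Bayesian result beside it.
- **(b)** Keep the Bayesian analysis as the main one, choose its decision rule, and replace the power and alpha sentence with the simulated probability of meeting that rule at 200 evaluable per arm under the reconciled rates.

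Under either option, report the posterior risk difference with a 95% credible interval, so that a Bayes factor is not read alone as showing an effect or its absence.

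The cost is wording in two paragraphs and, for (b), a short simulation; no extra participants or data are needed. The drawback is that the stated figure may become less favourable.
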